#### 4.1.4 Carboplatin dosing

If carboplatin is to be used, the dose uses target area under the curve of 5 and should be calculated according to the Calvert formula:

$$\text{Dose (in mg)} = \text{Target area under curve} \times (\text{GFR} + 25)$$

Carboplatin and etoposide will be given 3 weekly

## 4.2 THORACIC RADIOTHERAPY

Thoracic radiotherapy should start 21 days after day 1 of the first cycle of chemotherapy (day 22). A delay with the administration of the second cycle of chemotherapy **should not delay** the start of radiotherapy

### 4.2.1 Clinical assessment (see section 6.5)

Weekly assessments are required during treatment.

- Clinical examination
- Haematological assessments.

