### **4.3 TWICE DAILY THORACIC RADIOTHERAPY**

#### **4.3.1 Schedule**

- **45 Gy in 30 twice daily fractions** over a period of **19 days** (radiotherapy to start on a Monday), 5 consecutive days a week
- The optimal overall treatment time should be 19 days, up to 21 days is a protocol deviation and should be recorded, above 21 days is a protocol violation.
- The interfraction interval will be 6 to 8 hours.
- using conformal radiotherapy and 4 to 10 MV photons emitted from linear accelerators.

- Thoracic radiotherapy will start on cycle 1 day 22, if possible concurrently with the second cycle of chemotherapy (within 24 hours of day 1, cycle 2 of PE).
- Concurrent chemotherapy will be administered during the intervals between the 2 daily radiotherapy fractions.

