### 4.4 HIGH DOSE ONCE DAILY THORACIC RADIOTHERAPY

#### 4.4.1 Schedule

- **66 Gy in 33 daily fractions** over a period of **45 days** (radiotherapy to start on a Monday), 5 consecutive days a week
- The optimal overall treatment time should be 45 days. Up to 47 days is a protocol deviation and should be recorded, above 47 days is a protocol violation.
- using conformal radiotherapy and 4 to 10 MV photons emitted from linear accelerators.

- Thoracic radiotherapy will start on cycle 1 day 22, if possible concurrently with the second cycle of chemotherapy (within 24 hours of day 1, cycle 2 of PE).

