### **6.1 ASSESSMENTS DURING TREATMENT**

Please see section 4.0 for additional clinical visits required during treatment for each arm. During treatment the following information will be required and relevant details reported on case report forms (3-weekly):

- Clinical examination, performance status (see appendix 1), dyspnoea score (see appendix 3) and weight
- Haematology and biochemistry results
- Calculated creatinine clearance before each cycle of chemotherapy (see section 4.1.1)
- Details of any non cancer related treatment received
- Assessment of toxicity graded according to CTCAE v3.0 (see appendix 2)

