| PCI (if indicated)                    |                |                      |                                           |                                    |                                     | X c                                           |                                                                    |
| Adverse Events/Toxicities             | X              | X
(baseline)      | X                                         | X                                  | X                                   | X                                                        | X                                                                  |
| Radiation Toxicities                  |                |                      | X                                         | X                                  | X                                   | X                                                        | X                                                                  |
| Research blood specimen               |                | X (days 1 & 22)      |                                           |                                    |                                     | X                                                        | X (relapse)                                                        |
| Tumour sample                         |                | X                    |                                           |                                    |                                     |                                                          |                                                                    |

a Measured as per local policy but at a minimum of 3-weekly

b Cycle 1 of chemotherapy to start within 2 weeks of randomisation and assessment of clinical fitness

c PCI- to be performed a maximum of 6 weeks after chemotherapy completion

d Pleural aspiration/ cytology- to be performed if possible in patients with pleural effusion

e Screening chest/ upper abdo CT & screening brain CT/MR- to be performed within 4 weeks prior to randomisation

f Follow-up visit scheduling- weekly review until resolution of acute side effects, then 3-monthly until 1 year post randomisation, 6 monthly thereafter (or more frequently at discretion of the investigator)

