## 6.5 STUDY FORMS

|                                          |                                                                                                                                                                                                                                    |                            |
|------------------------------------------|------------------------------------------------------------------------------------------------------------------------------------------------------------------------------------------------------------------------------------|----------------------------|
| Eligibility checklist      | To be completed at the time of randomisation, prior to phoning the trials office.                                                                                                                                                  | Form Pre-a          |
| Pre-treatment form         | To be completed at baseline prior to cycle 1                                                                                                                                                                                       | Form Pre-b          |
| Tumour assessment form     | To be completed at baseline prior to cycle 1                                                                                                                                                                                       | Form Pre-c          |
| Treatment form             | To be completed on day 1 of each cycle. Data collection includes: protocol treatment(s) received, toxicity, reasons for reduction/delay/omission, performance status

Complete forms for all cycles (1-4 or 6) | Form A              |
| Toxicity form              | To be completed at the end of each cycle given, prior to next cycle and 30 days after completion of last cycle of chemotherapy

Complete forms post cycle to capture all data                                  | Form B              |
| Radiotherapy worksheet     | To be completed during and after completion of radiotherapy                                                                                                                                                                        | Form C              |

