**Safety profile**

The main toxicities associated with etoposide are:

**Gastrointestinal toxicity:** Nausea and vomiting are the major gastro-intestinal toxicities. The severity of such nausea and vomiting is generally mild to moderate with treatment discontinuation required in 1% of patients. Diarrhoea, anorexia and mucositis may occur. Constipation and swallowing disorder have been observed rarely.

**Haematotoxicity:** Myelosuppression is dose limiting, with granulocyte nadirs occurring 5 to 15 days after drug administration and platelet nadirs occurring 9 to 16 days after drug administration. Bone marrow recovery is usually complete by day 21, and no cumulative toxicity has been reported.

**Allergic reactions:** Seldom hypersensitivity reactions caused by benzyl alcohol may occur. Anaphylactic-like reactions characterised by flushing, tachycardia, bronchospasm, and hypotension have been reported (incidence 0.7-2%), also apnoea followed by spontaneous recurrence of breathing after withdrawal of etoposide infusion, increase in blood pressure. The reactions can be managed by cessation of the infusion and administration of pressor agents, corticosteroids, antihistamines and/or volume expanders as appropriate.

**Hypotension:** Transient hypotension following rapid intravenous administration has been reported in 1% to 2% of patients. It has not been associated with cardiac toxicity or electrocardiographic changes. To prevent this rare occurrence, it is recommended that etoposide is administered by slow intravenous infusion over a 30- to 60-minute period. If hypotension occurs, it usually responds to supportive therapy after cessation of the administration. When restarting the infusion, a slower administration rate should be used.

**Other toxicities:** Reversible alopecia, sometimes progressing to total baldness was observed in up to 70% of patients. The following adverse reactions have been infrequently reported: peripheral neuropathy, paresthesia, increased liver function tests with high doses, radiation "recall" dermatitis, hand-foot syndrome, central nervous effects (fatigue, drowsiness) 0-3%, hyperuricemia, taste impairment, fever, rash, urticaria, skin discoloration, pruritus, abdominal pain. The following adverse events have been reported after administration of etoposide (a causal relationship has not been established): Stevens-Johnson syndrome, rhythm disorders, myocardial infarction, reversible loss of vision.

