Toxicity will be assessed according to NCI Common Terminology Criteria for Adverse Events V.3.0. The proportion of patients experiencing a grade of 3 or above acute toxicity, including acute and/or late radiation morbidity, will be compared between the treatment groups using  $\chi^2$  and Fisher Exact tests. Acute toxicity will be defined as toxicities occurring from commencement to 3 months after completion of treatment; late toxicity will be defined as toxicities occurring between 3 months and 2 years after completion of treatment. All patients treated with at least one dose of cisplatin and etoposide will be evaluated for tumour response and included in the analysis of tumour response rates.

Response will be assessed according to Response Evaluation Criteria In Solid Tumours (RECIST) criteria. The proportion of patients in each treatment group whose best response (up to approximately 28 days post cycle 4 or, if stopped prior to cycle 4, approximately 28 days after last chemotherapy cycle given) from randomisation is complete or partial will be compared using  $\chi^2$  and Fisher Exact tests.

Safety analyses will be performed for all randomised patients treated with at least one dose of chemotherapy. Adverse effects will be summarised and compared between the two arms. The relative chemotherapy and RT dose intensity (RDI) will be summarised by calculating the median, SD, IQR and range for patients in each randomised treatment group. The RDI will be compared between the treatment groups by using the Wilcoxon Rank Sum test.

A detailed description of patient disposition will include a summary of the following:

- ▶ All patients entered and enrolled: overall, by treatment arm and by country
- ▶ Reasons for patients entered but not enrolled
- ▶ All enrolled patients treated with study drug, by treatment arm
- ▶ Reasons patients enrolled but not treated with study drug
- ▶ Reasons patients discontinued study drug treatment
- ▶ All important protocol violations.

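### Required blood counts follow the length of radiotherapy, so cycle 3 has two mid-cycle counts in the once-daily arm that the twice-daily arm lacks, and detection of symptomless grade 3+ laboratory toxicity is open to bias against once-daily

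*Supplement*

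**What the plan says.** Section 4.2.1 of the latest protocol sits under Thoracic Radiotherapy. It says "Weekly assessments are required during treatment" and lists clinical examination and haematology. Section 6.1 confirms that such visits come on top of the common schedule and can differ by arm: "Please see section 4.0 for additional clinical visits required during treatment for each arm".

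The two courses differ in length. For BD (section 4.3.1), "The optimal overall treatment time should be 19 days". For OD (section 4.4.1), "The optimal overall treatment time should be 45 days". Both start on day 22 (section 4.2).

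Outside radiotherapy, section 4.1.1 requires a full blood count before each cycle. Footnote a to the visit table in section 6.4 sets the floor for haematology during the additional cycles: "Measured as per local policy but at a minimum of 3-weekly". The table leaves haematology blank in both radiotherapy columns and in the follow-up column.

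Toxicity is recorded on Form B once per cycle and 30 days after the last cycle, with the instruction "Complete forms post cycle to capture all data" (section 6.5). The SAP compares "The proportion of patients experiencing a grade of 3 or above acute toxicity" between arms by chi-squared and Fisher exact tests. The window runs from the start of treatment to 3 months after its completion. Neither document mentions that required monitoring differs by arm.

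**The concern.** Toxicity is a secondary endpoint, and the toxicity of twice-daily treatment is part of the protocol's rationale for testing a once-daily schedule. A low neutrophil or platelet count without symptoms is recorded only if blood is taken while the count is low. For etoposide, Appendix 7 gives "granulocyte nadirs occurring 5 to 15 days after drug administration", platelet nadirs at 9 to 16 days, and recovery usually complete by day 21. Extra counts placed on the nadir in one arm only can therefore raise that arm's recorded grade 3+ rate when true toxicity is equal. Here the arm affected is OD.

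**Working it through.** **Reproducing the course lengths.** Treatment is on five days a week from a Monday.

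- BD: 30 fractions at two a day make 15 treatment days, ending on the Friday of week 3: 2 × 7 + 5 = day 19.
- OD: 33 treatment days end on the Wednesday of week 7: 6 × 7 + 3 = day 45.

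Both agree with the protocol. Starting on day 22, radiotherapy runs over days 22–40 (BD) and 22–66 (OD).

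**Required counts without delays.** Weekly counts fall on day 22 + 7k. Pre-cycle counts fall on days 1, 22, 43, 64 and so on.

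| | OD | BD |
|---|---|---|
| Weekly radiotherapy counts | 22, 29, 36, 43, 50, 57, 64 (7) | 22, 29, 36 (3) |
| With pre-cycle counts, days 22–66 | the same 7 | 22, 29, 36, 43, 64 (5) |
| All scheduled assessments to first 3-month follow-up, 4 cycles | 10 | 8 |
| The same, 6 cycles | 12 | 10 |

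The overall ratios are 10/8 = 1.25 and 12/10 = 1.20. The last two rows place the post-treatment visit 30 days after day 1 of the last cycle and the follow-up visit 90 days later. Leaving out that follow-up visit, at which no haematology is required, gives 9/7 = 1.29 and 11/9 = 1.22. The net difference is always two counts, on days 50 and 57.

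**Where those two counts fall.** Cycle 3 starts on day 43, with etoposide on days 43–45.

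- Etoposide granulocyte nadir: 43 + 5 to 45 + 15, or days 48–60.
- Etoposide platelet nadir: 43 + 9 to 45 + 16, or days 52–61.
- OD samples days 50 and 57. The next guaranteed BD count is day 64.
- Appendix 7 puts cisplatin platelet and leucocyte nadirs at days 18–23. Counting day 43 as day 1, that is days 60–65, so the day-64 count can catch some events in both arms.

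The other cycles are balanced. Neither arm has a required mid-cycle count in cycle 1, both have days 29 and 36 in cycle 2, and OD radiotherapy ends on day 66, two days into cycle 4.

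**Illustrative size (assumptions, not in the documents).** Let p be the chance of a grade 3+ nadir per cycle, equal in both arms, and ρ its within-patient correlation between cycles 2 and 3. If cycle 2 is fully detected in both arms and cycle 3 in OD only:

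- BD = p
- OD = 1 − [(1−p)² + ρp(1−p)]
- Excess = p(1−p)(1−ρ)

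| Excess in OD, percentage points | p = 0.2 | p = 0.3 | p = 0.5 |
|---|---|---|---|
| ρ = 0 | 16.0 | 21.0 | 25.0 |
| ρ = 0.3 | 11.2 | 14.7 | 17.5 |
| ρ = 0.6 | 6.4 | 8.4 | 10.0 |
| ρ = 0.8 | 3.2 | 4.2 | 5.0 |

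With 532/2 = 266 per arm, the normal approximation gives a 42–99% chance of a significant result at ρ = 0.3–0.6 and 14–21% at ρ = 0.8.

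These are upper bounds for each p and ρ. If the BD day-64 count catches a share f of cycle-3 events, and a share g of patients already have another recorded grade 3+ event (independently), the excess is multiplied by (1−f)(1−g). At p = 0.3 and ρ = 0.3–0.6:

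- f = 0, g = 0: 8.4–14.7 points, 54–94% chance of significance.
- f = 0, g = 0.5: 4.2–7.4 points, 18–45%.
- f = 0.5, g = 0.5: 2.1–3.7 points.

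**The case against.** A reader might infer from seven weekly radiotherapy visits against three that toxicity is looked for more than twice as often in OD, and that the comparison is therefore biased. The documents do not support that. Once pre-cycle counts are included the figures are seven and five, and over the wider period the ratio of assessments is about 1.2 to 1.3.

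Several further objections stand:

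- The three-weekly figure is a floor. Centres may count weekly in both arms, and a low pre-cycle count delays treatment until recovery, which implies repeat counts.
- Cisplatin nadirs fall close to the BD pre-cycle count, so zero BD detection in cycle 3 is an extreme assumption.
- The SAP describes the proportion of patients with grade 3+ acute toxicity. Patients already counted for another event cannot add to an excess.
- Section 6.1 asks for CRF details three-weekly, and the CRFs are not shown. Transfer of interim counts to Form B is an inference.
- Under section 4.1, cycle 3 is concurrent with radiotherapy in OD but not in BD. More OD myelosuppression in cycle 3 may be real, and an analysis that drops days 50 and 57 could hide it.

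Three objections do not remove the point. The weekly review after completion of treatment (section 6.2) lists no blood count. An equal number of toxicity forms does not equalise what is known when each is filled in. Reporting of grade 3–4 radiation oesophagitis and pneumonitis as serious adverse events (section 5.1) protects those outcomes, but not a symptomless low count.

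**Conclusion.** The point holds in a limited form. Under the minimum schedule, OD has two required mid-cycle counts in cycle 3 that BD lacks, and they fall on the etoposide nadir. The comparison of transient, symptomless grade 3+ laboratory toxicity is open to bias against OD, and the plan does not address it.

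The documents do not fix the size. It depends on local count policy, on whether interim counts reach Form B, and on how many events the BD count at about day 64 catches. It is diluted in a composite of any grade 3+ toxicity. The tabulated excesses rest on assumed rates and correlations, with perfect OD and no BD detection in cycle 3. They should not be read as estimates. Overall survival is untouched, as are symptomatic oesophagitis and pneumonitis.

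**What to change.** Keep the planned any-time comparison and add to the SAP:

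1. A sensitivity comparison of haematological grade 3+ toxicity, where dated counts are held. Limit it to counts required in both arms (before each cycle, at end of treatment, and weekly on days 22–40), plus clinically declared events such as febrile neutropenia, bleeding or transfusion.
2. Separate reporting of haematological and non-haematological grade 3+ toxicity.
3. The number of counts per patient by arm.

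The restricted comparison should stay a sensitivity analysis, because OD cycle 3 may truly be more myelosuppressive. If the two analyses differ, the counts per patient help the reader judge how far detection could explain it.

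If recruitment is still open, section 4.2.1 could set one calendar window for weekly counts in both arms, for example days 22 to 66.

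The SAP change costs some wording and one extra derivation. The schedule change costs about two extra routine counts per BD patient.

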### 4.2.2 General radiotherapy details

Patients should be treated on a linear accelerator operating at 4-10 MV.

The total dose of radiotherapy will be

- BD arm: 45 Gy in 30 twice daily fractions of 1.5 Gy
- OD arm: 66 Gy in 33 daily fractions of 2 Gy

The total dose is prescribed at the ICRU reference point and given according to the recommendations of the EORTC radiotherapy group (25) and ICRU 50 (26). Treatment will be planned with inhomogeneity corrections.

IMRT will be permitted for the centres routinely using it for the treatment of lung cancer.

#### i. Radiation Quality Assurance:

The radiotherapy quality assurance program will be run by the Mount Vernon Hospital QA team (appendix 10). Planning information, copies of portal images (digital print-outs are acceptable) and dose distribution, including Dose Volume Histogram (DVH), with a copy of the treatment prescription should be available for central review. Details of radiotherapy practice will be established by completion of a questionnaire.

Treatment machine beam output data on the linear accelerators used to treat patients in the trial should have been audited by a recognised ASTRO/ESTRO or UK quality assurance programme within 12 months of the first patient in the centre entering the trial, and be rechecked at least once every 18 months

We recommend that daily verifications should be done with open orthogonal images incorporating stable anatomical structures such as the spine for the first 3 days of treatment followed by weekly verifications. If available cone beam imaging can be used as an alternative to open orthogonal images. The orthogonal images will be checked by a senior radiographer and if possible reviewed by a qualified radiation oncologist, and compared with either the digitally reconstructed images or simulator images. The correction decision will be left to local policy. Differences of less than 0.5 cm from the initial images will be allowed. We suggest that if the difference is more than 0.5 cm the orthogonal images will be repeated prior to patients treatment. The Radiotherapy Quality Assurance Group will approve and monitor each centre procedures.

#### **ii. Patient treatment position:**

Supine, with arms above head. Immobilisation using chest board and fixed arm position. The patient should be breathing normally.

#### **iii. Patient data acquisition:**

A planning CT scan should be performed in the treatment position, whilst the patient undertakes a normal respiration, using 5 mm slices or less through the entire target volume. The whole thorax (cricoid to L2) should be covered using at least 1 cm slices to allow dose-volume histograms to be calculated for the lung, heart and the oesophagus.

Radiotherapy should be started within 3 weeks of planning.

#### **iv. Planning target volume (PTV)**

The CT data will be transferred to the planning system.

- The GTV (gross tumour volume) will be contoured by a qualified radiation oncologist specialised in thoracic malignancies. The contouring should be carried out using the mediastinal and the lung windows. The GTV is defined as identifiable tumour and involved lymph nodes (nodal involvement on CT scan is defined as nodes  $\geq 1$  cm in short axis). If PET scan is available for staging, the GTV should include PET positive lymph nodes.
- The CTV (clinical target volume) comprises the GTV with a 0.5 cm margin of radiologically normal tissue in all directions. It will take into account microscopic spread. Manual adjustment of CTV is permitted to reduce dose to the spinal cord for example, when disease is adjacent to a structure such as a vertebra but is not thought to invade the structure
- The PTV comprises the CTV with a 1 cm margin superiorly and inferiorly, and 0.8 cm margin laterally, at the 95% isodose. The CTV to PTV expansion should not be reduced as it is allowing for set up errors and organ motion.

Prophylactic nodal irradiation should not be employed.

Field reductions will not be allowed.

